**Figure 4 F4:**
[figure not shown]
The figure describes the trial schedule from patients enrollment to trial close-out.

### Adverse events

2.15

Before the enrollment of the study, the participants or the patient's legal guardian will be informed about acupuncture adverse events including bleeding, hematoma, infections, alcohol allergy, pneumothorax, etc. In any case of acupuncture related serious adverse events occurring, these will be reported immediately to the primary investigator and the institutional review board. We will collect all the adverse event details such as: treatment site, acupuncture points selected, patient recovery outcome, number of events, etc. Acupuncture will be stopped and treatment groups will be un-blinded. We will also provide suitable treatment, including hospitalization for the patients.

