## Introduction

1

The rib cage and associated anatomical structures are responsible for protecting the vital organs located within the chest cavity.^[1]^ The occurrence of blunt chest trauma (BCT) typically involves multiple levels of injury including heart rupture, aortic dissection, lung contusion, rib fracture, or simple soft tissue injury. In the case of preserved organ function, it is the bony structures and soft tissues which are most commonly affected by BCT injury.^[1]^ According to previous literature, BCT patients can be divided into 3 levels based on the severity of injury as identified by chest plain film findings. Level 1 includes patients without rib fractures; level 2 includes patients with 1 or 2 rib fractures; and level 3 includes patients with more than 2 rib fractures.^[2]^ Based on retrospective studies, level 3 patients experience increased frequency of hospitalization, thoracotomies, and a higher mortality rate. Levels 1 and 2 patients are commonly treated as out-patients, but still suffer greatly from chest pain and tend to experience breathing difficulties.^[2,3]^ The pain associated with the BCT injury may in turn lead to the inability have sufficient sleep, with the resultant lack of rest impeding the recovery process.^[4]^ The most commonly used conventional treatments are analgesics.^[1,5]^ Moreover, while nerve block surgical intervention is also practiced as a treatment intervention, it is commonly reserved for level 3 patients experiencing severe pain and/or thoracic deformity.^[1,5]^ While analgesic medication can relieve pain temporarily, most patients still suffer prolonged nociceptive hypersensitivity and usually have difficulties in performing daily life activities for sometime after. Furthermore, elderly and renal insufficiency patients are at a higher risk of experiencing harmful effects from long term use of analgesics and muscle relaxants.^[6]^

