### Drug treatment

2.12

Both groups of participates will also receive the prescribed analgeasic medication and/or muscle relaxants. The frequency of the prescribed medicine is 3 to 4 times a day along with meals and before sleep for 7 days. The purpose of the medication is for pain relief, therefore, the participants can discontinue the medication at will.

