### Follow-up

2.14

After the initial visit to the chest surgical out-patient clinic, the participates in both the Acu and Con groups will be expected to return 4 days after acupuncture/placebo treatments for needles/placebos withdrawal along with chest plain film, NRS, FRS scores, flowmeter, respiratory function, VSH sleep scale assessments, and amount of medication used. On the 14th day and at 3 months after the initial intervention, a study personal will arrange a telephonic consultation to enquire about the pain scale (NRS) and any adverse effect related to the acupuncture treatment and the chest trauma (Fig. 4).

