
### Limitations

3.1

The study provides an effective intervention but is limited to a shallow acupuncture needling depth of the superficial subcutaneous layers and cannot be associated with the benefits caused by the deeper stimulations commonly associated with most acupuncture interventions. Furthermore, the point selection in this study only concentrates on anterior and lateral BCT locations. Lastly, the follow-up method of telephone calls at 14 days and after 3 months can prove problematic, and a high loss to follow-up is anticipated.

In this study, we offer a simple, low-cost form of acupuncture that, if it will prove superior analgesic effects in comparison to the placebo, can provide a safe and reasonable treatment alternative to BCT patients.

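### The stated adverse-event rules select events by presumed cause before recording, so no stated enquiry covers effects of the analgesics and muscle relaxants given to both arms

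*Protocol article*

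**What the plan says.** Section 2.14 (Follow-up) gives the content of the telephone calls at day 14 and 3 months, in both groups: the pain score and "any adverse effect related to the acupuncture treatment and the chest trauma". For the day-4 visit the same section lists removal of the tacks or placebos together with "chest plain film, NRS, FRS scores, flowmeter, respiratory function, VSH sleep scale assessments, and amount of medication used"; that list names no adverse-event question.

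Section 2.15 (Adverse events) sets the reporting rule: "In any case of acupuncture related serious adverse events occurring, these will be reported immediately to the primary investigator and the institutional review board". The next sentence concerns collection: "We will collect all the adverse event details such as: treatment site, acupuncture points selected, patient recovery outcome, number of events, etc".

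Section 2.12 (Drug treatment) sets a co-treatment: "Both groups of participates will also receive the prescribed analgeasic medication and/or muscle relaxants", taken "3 to 4 times a day along with meals and before sleep for 7 days", which patients may stop when they wish. Section 2.13 measures how much of it was used, as a secondary outcome. The Introduction gives part of the rationale: "elderly and renal insufficiency patients are at a higher risk of experiencing harmful effects from long term use of analgesics and muscle relaxants". Section 3.1 (Limitations) closes by saying that the intervention, if its analgesic effect proves superior to placebo, "can provide a safe and reasonable treatment alternative to BCT patients".

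**The concern.** In a blinded randomised trial the most dependable safety comparison is the count of all adverse events by arm, whatever their supposed cause. Randomisation makes it unnecessary to guess the cause of each event. A rule that asks only about events already linked to particular causes brings the guess back, and does so before anything is written down.

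The guess is hard here. Tack, drug and injury act in the same patient over the same days, and section 2.7 blinds the patients, the acupuncturist and the nurse who measures outcomes. A symptom such as dizziness or nausea (my example, not the protocol's) could be assigned to any of the three.

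The cause that the enquiry leaves out is a planned exposure in both arms. The trial counts the medication but states no question about its effects. If acupuncture reduces medication use, any accompanying reduction in drug effects could not be shown from the stated enquiry. An event that was never recorded cannot be recovered at the analysis.

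**Working it through.** The plan gives no figure to reproduce, so the check is a comparison of texts, followed by one calculation for context.

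**1. Each rule set against the presumed cause.** The last two columns take the two possible readings of the collection sentence in section 2.15.

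| Event attributed to | 2.14 calls ask for it | 2.15 immediate reporting if serious | 2.15 details collected, narrow reading | 2.15 details collected, wide reading |
|---|---|---|---|---|
| Acupuncture | yes | yes | yes | yes |
| Chest trauma | yes | no | no | yes |
| Analgesic or muscle relaxant | no | no | no | yes |
| Other or unclear | no | no | no | yes |

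The narrow reading takes the sentence as describing the acupuncture-related events just mentioned; its examples (site of treatment, points used) favour it. The wide reading takes it as covering every adverse event.

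- Narrow reading: drug-attributed events fall outside every stated rule.
- Wide reading: section 2.15 promises to collect events that the enquiry in section 2.14 does not ask for, so the two sections conflict.

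Either way the text needs correction.

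**2. What the enquiry depends on.** The calls carry the only stated question, and section 3.1 expects substantial loss to follow-up for those calls. If the medication starts on the day of the intervention (an assumption), the first call comes 14 − 7 = 7 days after the prescribed course ends. The day-4 visit falls inside the course, but its listed content includes no adverse-event question.

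**3. Direction of any effect.** Both arms get the same question, and patients and the outcome nurse are blinded. The filter therefore removes events under the same rule in each arm. Nothing in the document shows that it removes more from one arm than from the other.

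**4. Scale of any safety statement.** Inputs: 36 patients per group (section 2.16), and 29 per group, the size of the earlier study cited there, which is also about what remains after the stated 20% dropout (36 × 0.8 = 28.8). With no events in n patients, the exact one-sided 95% upper limit for the event rate is 1 − 0.05^(1/n).

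- n = 36: 1 − 0.05^(1/36) = 0.080, or 8.0%.
- n = 29: 1 − 0.05^(1/29) = 0.098, or 9.8%.

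These limits assume complete capture. They do not measure the defect and would not change with the correction. They show only how modest a safety statement must be at this trial size, even when every event is recorded.

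**The case against.** The best defence is that this is a condensed article and that several stronger charges do not follow from it. Most of that defence stands.

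- *Drug effects are never asked about.* A reader might infer this, but it is not proven. The collection sentence in section 2.15 may mean all events. The trial schedule is in Figure 4, which was not available to this review, and the day-4 list does not show that nothing is asked when patients attend in person and return unused medication. Section 2.19 also names pulmonary complications and hospital admission as subgroup factors without a causal filter, so some unfiltered events must be recorded.
- *The serious-event sentence restricts what patients are asked.* It does not. It governs immediate reporting; the restriction on enquiry is in section 2.14.
- *The filter biases the comparison.* It is the same in both blinded arms, and no differential effect can be shown.
- *The trial ignores the drug harm on which its rationale rests.* The Introduction speaks of long-term use, whereas the course is 7 days, and reducing drug harm is not a stated objective.
- *The trial plans to conclude that acupuncture is safe.* Section 3.1 offers a conditional prospect, not a planned safety conclusion. The absence of a safety analysis in section 2.19 may be made good in a fuller document.

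The defence does not answer the stated wording. Section 2.14 contains a rule, not a gap. Followed literally, it puts attribution before recording and leaves out one planned exposure.

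**Conclusion.** The point holds as a cheap improvement to a stated rule. The only adverse-event enquiry that the article describes is limited by presumed cause, and immediate reporting is limited further, to acupuncture-related serious events. No stated enquiry covers effects of the medication that both arms receive. The collection sentence in section 2.15 either shares this limit or contradicts section 2.14.

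The consequence is lost events and dependence on guessed causality. How many events would be lost cannot be calculated from the document. The verdict rests on reading section 2.14 as the wording that staff will follow; if the full protocol already has an open question, only the article's text needs correcting. The word *safe* in section 3.1 depends there on analgesic superiority alone, which is not evidence of safety.

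**What to change.** Reconcile sections 2.14 and 2.15 along these lines: patients in both arms are asked the same open question about any new or worsened health problem; every event reported is recorded first; relatedness to acupuncture, medication or trauma is then recorded as a separate attribute. State that all serious events are reported to the investigator and the review board whatever the presumed cause. Compare all-cause events by arm, with exact confidence intervals.

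Section 2.15 also mentions stopping acupuncture and unblinding. Once the range of recorded and reported events is wider, the authors need to say which events that sentence covers; no rule is proposed here.

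In section 3.1, limit the word *safe* to what the all-cause comparison supports, given upper limits of about 8% to 10% even with no events in an arm.

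The cost is a change of wording in the protocol and the case report form, slightly more event recording and a more modest safety statement. Sample size and visit schedule are unaffected.

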### Sample size calculation

2.16

In a previous similar study,^[11]^ the pain scale reduced significantly as recorded immediately after acupuncture treatment. We utilized the result of this study to calculate sample size as generated by G∗power version 3.1.9.2 software. Accordingly, in the condition of 95% power being calculated with an effect size of 1.124365. The patient number in each group should be a minimum of 18 participants. However, we also considered that a previous study included 29 patients in each group with a total of 58 patients. With respect to a dropout rate of 20%, we decided to include 36 patients in each group, for a total of 72 patients.

### Quality control/data management

2.17

To maintain the integrity of the study, all the recorded data and documents will be recorded manually as a personal file first and restored in both paper and electronic form. All the documents will be stored in a secure location in the chest surgical department of China Medical University Hospital, and will be destroyed after 5 years of trial completion. Access to patient data will be restricted to study medical personals. We will also arrange regular meetings to gather the entire study personnel, including the primary investigator, the acupuncturist, study nurses, and chest surgeons, in order ensure the integrity of the study protocol and due process. Any modification in the study protocol will be done upon agreement with the China Medical University Hospital institutional review board.

### Dissemination

2.18

After the completion of the study, we plan to publish the results and the study data in a medical journal.

### Statistical analysis

2.19

Statistical analyses will be performed using SPSS software version 22.0 (SPSS Inc, Chicago, IL). The demographic data between Acu and Con groups including gender, age, and clinical characteristics will be compared using the Student's *t* test and Chi-squared test. Between-group values will be measured by the paired *t* test. For the multiple pain scale and sleeping quality measurements, a one-way ANOVA will be used according to the previous similar study.^[11]^ We will also implement the advanced repeat measurement analysis in the study. Data will be presented as mean ± standard deviation. A *P*-value of less than .05 will be considered statistically significant.

Subgroup analysis will be done based on the following: age, sex, number of treatments complete, number of hours of needle retention, number of rib fractures, pulmonary complications, hospitalization, number of days from patient's injury to the first treatment, Triflow score, medication use, body mass index, and ISS. In cases of small sample size, the Mann–Whitney *U* and the Wilcoxon sign rank test will be implemented accordingly. Missing data will be analyzed using the pairwise deletion method.

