### Design and setting

2.1

The study is designed as a single-center randomized control, parallel-arm, double-blinded trial. It will take place in the out-patient clinic of China Medical University Hospital. The study will be conducted from March 2020 to March 2022. The study was approved by the institutional review board of China Medical University Hospital (CMUH109-REC1-002), and was registered on clinicaltirl.gov (NCT04318496).

The main goal of the study is to reduce pain and improve the respiratory function and sleep quality of patients after BCT. The participants will be divided to 2 groups; acupuncture group (Acu) who will receive the true press tack needles, and a placebo group (Con) who will receive press tack placebos on the same acupoints without the needle element. Patient outcome measurements include: Numerical Rating Scale (NRS), Face Rating Scale (FRS), respiratory function flowmeter Verran Snyder-Halpern sleep scale (VSH), and the total amount of allopathic medication used.

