### Randomization and allocation concealment

2.6

The participants will be randomized into 2 groups with a 1:1 ratio produced by the SPSS program software, version 22. A computer-based simple random sampling with a 1:1 ratio without stratification will be used. A number (1–72) will be affiliated to each patient at the time of their first visit to the out-patient clinic and after completing the informed consent. The number, patient name, and date of birth will be written down on a non-transparent envelope by a study nurse 1 (researcher [name]). Inside the envelopes, there will be 14 separate sterile press tack needles or identical looking press tack placebos. The envelopes in both groups will appear identical. Study nurse 1 will write down the number, patient name, and intervention in an electronic chart and create a file for each patient.

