## Discussion

3

The nociceptive response is a reflexive bodily response of the body aimed at providing protective mechanisms. In short, pain creates awareness of pathological conditions resultant from injury or harm, and may vary in intensity, quality, duration, and referral. Accordingly, pain is categorized according to 4 distinct types: nociceptive pain, inflammatory pain, neuropathic pain, and functional pain.^[12]^ In the case of BCT, nociceptive signals are transmitted to the brain following peripheral tissue damage. In terms of the 1 to 10 NRS pain scale, the patient's pain levels on the first recorded day of injury can reach up to 9 to 10 points, whereafter the pain sensation gradually decreases and is subsequently recorded at reduced levels of 2 to 3 points after 15 days.^[13]^ However, the long term effects of pain resultant from physical injury usually display concurrent overlapping conditions related to the physical, psychological, and even socio-economic function ability of patients, and can last up 12 months after initial injury.^[14]^

Acupuncture treatment is well known for its analgesic potential, with proven efficacy particularly in chronic pain conditions. Furthermore, the therapeutic benefits of this treatment are extended to complicated conditions of maladaptive pain, such as myofascial pain, tension headache, irritable bowel syndrome, etc.^[15–19]^ In terms of acute pain, acupuncture has displayed promising analgesic effects in a wide array of diseases, with particular emphasis on emergency medicine.^[20–22]^ Furthermore, acupuncture has displayed tendencies of increased efficacy in the treatment of bone fractures as shown in elders in the acute stage of hip fracture. In addition, patients who received acupuncture treatment in the ambulance en route to hospital, reported reduced pain sensations, less anxiety, and lower heart rates. They also stated a higher overall satisfaction regarding the emergency ride to the hospital.^[22]^

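### Section 2.19 assigns a paired t test to the comparison of two independent arms, and no other named analysis is made the treatment test in its place

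*Protocol article*

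**What the plan says.** Protocol article, section 2.1: "The study is designed as a single-center randomized control, parallel-arm, double-blinded trial". Section 2.6 on allocation: "A computer-based simple random sampling with a 1:1 ratio without stratification will be used". Neither section mentions matching.

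Section 2.19 gives the tests. Student's t test and the chi-squared test are named for demographic and clinical characteristics. For the comparison of arms it says "Between-group values will be measured by the paired" t test. It continues: "For the multiple pain scale and sleeping quality measurements, a one-way ANOVA will be used according to the previous similar study". It then adds "We will also implement the advanced repeat measurement analysis in the study", with no model, factors or rank among the analyses. For small samples it names the Mann-Whitney U test, and "Wilcoxon sign rank test will be implemented accordingly".

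Section 2.13 schedules pain before treatment, at 30 minutes and at day 4, with NRS also at 14 days and 3 months. That makes three scores per patient, or five for NRS. The sleep scale is completed twice.

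**The concern.** A paired t test needs a natural partner for each observation. In a parallel-arm trial with unmatched randomisation, an Acu patient has no partner in Con. The sentence therefore names a test that cannot be carried out as described without inventing pairs, or else one that answers a different question (change over time within an arm).

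The ANOVA sentence raises a second difficulty. One-way ANOVA assumes independent observations, and repeated scores from one patient are not independent. Whether this matters depends on the factor and on which scores enter, and neither is stated.

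At stake is the efficacy claim itself. The protocol lists three kinds of analysis for the outcomes and does not say which one compares the arms. A significant fall within Acu could then be reported as efficacy, or the most favourable of several p-values could be chosen after the results are seen.

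**Working it through.** **1. The plan's own figure.** Section 2.16 gives effect size 1.124365, power 95% and a minimum of 18 per group; section 2.19 gives alpha 0.05. For two independent means, n per group = 2(z_alpha + z_beta)² / d².
- One-sided: 2(1.645 + 1.645)² / 1.124365² = 17.1, so 18. The exact t calculation also gives 18 (power 95.15%).
- Two-sided: 2(1.960 + 1.645)² / 1.124365² = 20.6, so 21; exact t gives 22. At 18 per group the two-sided power is 90.6%.
- Paired t test, taking 1.124365 as the standardised mean difference of pairs: 11 pairs one-sided, 13 two-sided.

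The 18 reproduces from an unpaired, one-sided test and not from a paired one. The sample-size section and the analysis section imply different tests.

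**2. Paired test across arms, with pairs made by listing order.**
- Type I error: about 5% (simulated 4.8-5.1%).
- Degrees of freedom: n - 1 against 2n - 2; with 29 per arm, 28 against 56. Power at an assumed d = 0.75 is 78.7% against 80.1%, a small loss.
- Dependence on ordering: at an assumed d = 0.5 and 28 per arm (36 × 0.8 = 28.8, rounded down), the paired and independent tests disagree on significance in about 6% of simulated trials.
- Unequal arms: if the 72 allocations were independent 1:1 draws, the chance of exactly 36:36 is C(72,36)/2^72 = 9.4%. If pairs were fixed in advance and 20% dropped out independently, 36 × 0.8 × 0.8 = 23 complete pairs would remain, against about 29 per arm for an independent test.

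**3. Paired test within an arm.** This tests whether the mean change is zero, not whether the arms differ. The Discussion (section 3) describes pain after blunt chest trauma as "subsequently recorded at reduced levels of 2 to 3 points after 15 days", and section 2.12 gives both arms analgesics and/or muscle relaxants. A fall is therefore expected in both arms. As an illustration with assumed values: SD 2, within-patient correlation r, SD of change = 2√(2(1 - r)), 29 patients and no treatment effect. A mean fall of 1 point is then significant in 59%, 74% and 92% of arms at r = 0.3, 0.5 and 0.7.

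**4. One-way ANOVA.** There are three possible readings.
- *By arm at one time point:* F = t² of the independent t test. Valid.
- *By arm, pooling k scores per patient:* the variance of the arm difference is understated by about 1 + (k - 1)r, so the true two-sided size is about 2Φ(-1.96 / √(1 + (k - 1)r)).

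| k | r = 0.3 | r = 0.5 | r = 0.7 |
|---|---|---|---|
| 3 | 1.96/√1.6 = 1.55, 12% | 1.96/√2.0 = 1.39, 17% | 1.96/√2.4 = 1.27, 21% |
| 5 | 1.96/√2.2 = 1.32, 19% | 1.96/√3.0 = 1.13, 26% | 1.96/√3.8 = 1.01, 31% |

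  Simulation gives the same picture, about 12-20% for 3 scores and 18-32% for 5, with differences of a point or so between runs. Equal correlation between all times is assumed. These rows concern pain; sleep has only two scores.
- *Across time within an arm:* there is no Acu-Con contrast. The test also ignores the within-patient correlation, so its size with no change over time falls to 0.05-1.4% (3 scores, r 0.7 down to 0.3).

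**5. Does the sample size survive the correction?** With 29 completers per arm and a two-sided independent t test, power at d = 1.124365 is 98.8%. It does.

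**The case against.** The best defence is that the paired sentence is a slip. The small-sample fallback lists Mann-Whitney U and Wilcoxon signed rank side by side, which suggests that the authors had an independent comparison in mind between arms and a paired one within arms. The plan also includes a repeated-measures analysis which, with an arm-by-time term, would be a sound treatment comparison; model terms are commonly left to an analysis plan.

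Much of this stands as a reading of intent. It does not repair the text. Student's t test is named only for demographic and clinical characteristics, the outcome comparison is given the paired test, and the repeated-measures analysis comes in addition, without being named as the treatment test.

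Four stronger readings are tempting, and the documents do not support them.
- *That the ANOVA is invalid outright.* No factor is named, and by arm at one time point it is valid. The inflated error rates arise only if time points are pooled, which section 2.19 does not state.
- *That the paired test inflates false positives.* Across arms its size stays near 5%. The faults are arbitrariness and waste.
- *That pain falls steeply without treatment by the protocol's own figures.* The Discussion gives an upper limit for the first recorded day, not a mean, and does not say that those patients were untreated. A daily rate of natural recovery cannot be read from it.
- *That omitting baseline adjustment is an error.* An unadjusted randomised comparison is valid and only less precise. Covariates are often left to the analysis plan, and the repeated-measures analysis may include the pre-treatment score.

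**Conclusion.** Wrong as written, on one stated rule: a paired t test is assigned to the comparison of two independent, unmatched arms, and this conflicts with the unpaired basis of the sample size. It must be corrected because the efficacy claim rests on that comparison. The numerical damage from pairing across arms is modest: about 6% of trials change significance (d = 0.5 and 28 per arm assumed), with a small loss of power and patients lost from unequal arms. The larger risk is interpretive, if the test is used within arms and a fall that is expected in both is taken as a treatment effect.

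The ANOVA is under-specified, not wrong in every reading. Its 12-20% and 18-32% error rates are conditional on pooling and on an assumed correlation of 0.3-0.7. The planned repeated-measures analysis softens the defect without removing it.

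**What to change.** In section 2.19:
- Delete the between-group paired t test.
- State the Acu-Con difference as the efficacy test. Use the repeated-measures analysis already planned, with arm, time and arm-by-time terms, and name the pain score and the time point at which the arms are compared. Alternatively, use an independent-samples t test or ANCOVA at one named pain score and time point.
- Restrict any one-way ANOVA to a between-arm comparison at a single time point, or drop it.
- Report paired within-arm change as description only.
- State whether the test is one- or two-sided, since the 18 per group implies one-sided.

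As a recommendation and not a correction, adjust for the pre-treatment score, which is already collected. Residual variance is multiplied by 1 - r²: 0.91, 0.75 and 0.51 at assumed r of 0.3, 0.5 and 0.7, so a 25% reduction at r = 0.5.

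The 72 patients, the data collected and the software are unchanged. The cost is revised wording, with the institutional review board agreement that section 2.17 requires for protocol changes.

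### Section 2.19 gives the pain scales both a one-way ANOVA and a repeated-measures analysis, each read at P<.05, without saying which one decides superiority

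*Protocol article*

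**What the plan says.** Section 2.19 covers the pain outcome in three steps.

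- It assigns a method to the pain and sleep scales: "For the multiple pain scale and sleeping quality measurements, a one-way ANOVA will be used according to the previous similar study".
- It adds a second analysis without giving its model, outcome or contrast: "We will also implement the advanced repeat measurement analysis in the study".
- It sets one threshold for everything: "A *P*-value of less than .05 will be considered statistically significant".

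Two other sentences in the section bear on the point. A general one covers comparisons of the arms: "Between-group values will be measured by the paired *t* test". The paragraph on subgroups provides for rank tests, introduced by "In cases of small sample size", with no size given.

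Section 2.13 makes pain the main outcome. Pain scores are taken at three clinic times (before treatment, at 30 minutes and on day 4), and the NRS is also taken by telephone at 14 days and 3 months. The introduction hypothesises a superior analgesic effect over placebo, and section 3.1 returns to that aim: "if it will prove superior analgesic effects in comparison to the placebo". Neither 2.13 nor 2.19 says which analysis answers it.

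**The concern.** A 5% threshold describes the risk of a false superiority claim only if the deciding test is fixed beforehand. Here two analyses of the same scores are planned side by side. In a two-arm trial, a one-way ANOVA at one time point compares the arm means at that time. A repeated-measures analysis uses all the time points, and its group-by-time test asks whether the arms change differently. The two overlap because they share data, but they can give different answers. With no ranking, either could be presented as the result after the data are seen.

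Two things are at stake: the error rate attached to the main claim, and how the trial is to be read when one analysis is significant and the other is not.

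**Working it through.** **Inputs from the article.** Two arms, 1:1 (section 2.6). 36 per arm enrolled with 20% dropout (section 2.16), so 36 × 0.80 = 28.8, or about 29 completers. Threshold .05 (section 2.19). Three clinic times for pain (section 2.13).

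**Assumptions, not in the article.** Whole-number scores from 0 to 10, mean 5, SD 2; the same correlation between any two times (0.3, 0.5 or 0.7); two-sided tests; no true difference between arms; arm as the factor of the one-way ANOVA.

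**Step 1: bounds.** Two tests at 5% have a joint false-positive rate between 5% (complete overlap) and 5% + 5% = 10% (no overlap). Independence would give 1 − 0.95² = 9.75%.

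**Step 2: simulation.** 8,000 null trials per setting. Test A is the one-way ANOVA on the day-4 score. Test B is the repeated-measures group-by-time F test over the three clinic times. The share in which exactly one test is significant follows from the other columns: both = A + B − either, and exactly one = either − both.

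| Per arm | Correlation | A alone | B alone | A or B | Exactly one |
|---|---|---|---|---|---|
| 29 | 0.3 | 4.94% | 4.74% | 8.36% | 7.04% |
| 29 | 0.5 | 4.95% | 4.84% | 9.10% | 8.41% |
| 29 | 0.7 | 5.11% | 5.82% | 10.13% | 9.33% |
| 36 | 0.3 | 5.38% | 4.82% | 9.10% | 8.00% |
| 36 | 0.5 | 4.74% | 5.06% | 9.05% | 8.30% |
| 36 | 0.7 | 5.06% | 4.69% | 9.19% | 8.63% |

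First row: both = 4.94 + 4.74 − 8.36 = 1.32%; exactly one = 8.36 − 1.32 = 7.04%.

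Each test alone reproduces the stated 5% closely. The simulation error of an either-test rate near 9% is √(0.09 × 0.91 / 8,000) = 0.3 percentage points. The 10.13% lies just above the 10% bound because test B alone came out at 5.82% in that setting. Five time points give the same range of about 8-10%.

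**Step 3: the t test and the rank tests.** With two arms at one time point, F = t², so an unpaired t test and the one-way ANOVA have the same P value (0.1066 for both in a trial run). Allowing a choice between that test and Mann-Whitney gives 5.5-6.1% in the settings above, and about 5.4-6.5% in a separate run. This adds little.

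**The case against.** **The article is condensed, and the choice of a decisive model is often left to an analysis plan.** That is true, and silence would not be a finding. But the article is not silent. It names two methods for the same scales and joins them with an also. An unseen plan may rank them, in which case the published text needs to agree with it. Reading the added analysis as merely supportive is possible, but the text does not say so.

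**A reader might infer more:** that a t test, an ANOVA, a repeated-measures analysis and a rank test give three or four P values for one score at one time, with an error rate of 11-13.5%. The documents do not support this.

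- A correctly specified t test and the ANOVA are one test here, and the Student's t test in 2.19 is for demographic data.
- The sentence on the paired t test is general, while the next one assigns the pain scales to ANOVA. Whether a paired test suits independent arms is a separate question.
- The rank tests are a conditional replacement, placed after the list of subgroups, where small samples would arise.
- Most of the inflation comes from the repeated-measures tests, which pool time points. They are further tests of the scale, not of its day-4 value. The figures above 11% also count the repeated-measures group main effect.

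**No sentence says that any significant test suffices.** This stands. Such a rule is inferred from the missing hierarchy, and the closing remark in section 3.1 is not a decision criterion. The error rate is therefore conditional.

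**The factor of the ANOVA is not stated.** If it were time within an arm, the ANOVA would not test superiority and the 8-10% would not apply. The text would still need to say so.

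**Conclusion.** The point holds for two methods. Section 2.19 assigns a one-way ANOVA and a repeated-measures analysis to the same pain scale, reads both at P<.05 and ranks neither. If either may decide, the false-positive rate for one pain scale is about 8-10%, up to twice the stated level. In 7-9% of null trials exactly one of the two is significant, and the plan has no rule for that case. The size rests on the assumed score distribution and correlations and on arm being the ANOVA factor. It does not count the several scales, states and time points, which are a separate source of multiplicity. It is worth correcting because it affects the main claim and the correction is cheap.

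**What to change.** In 2.19, name one decisive analysis of the main pain outcome: a longitudinal model with arm, time and arm-by-time, using one between-arm contrast stated in advance and reported as a difference with its 95% CI. State that the one-way ANOVA and any t or rank tests of the pain scores are sensitivity analyses that cannot establish superiority. This brings the false-positive rate for that comparison back to about 5%.

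The cost is a wording change before unblinding, with no new data and no change in sample size. The downside is that a significant result from a non-decisive method can no longer be claimed as superiority.
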